#### 11.5 Monitoring adherence and safety

At enrollment, HIV-1 testing will be performed for HIV-1 uninfected partners, to confirm eligibility (HIV-1 seronegative at the time of study start). Couples will be counseled about ART and PrEP. HIV-1 uninfected partners will be offered PrEP; HIV-1 infected partners will be counseled about ART guidelines and will be offered TasP, or referred/initiated on ART if they are eligible at the time of enrollment. HIV-1 infected partners will continued to be counseled on the use of TasP as long as (s)he is eligible to use TasP during the study period. HIV-1 uninfected partners who have symptoms potentially consistent with acute HIV-1 infection (fever, rash, pharyngitis) will have enrollment deferred for 2 weeks at which time repeat serologic testing will be performed (and, if positive, will result in study exclusion).

Adherence, risk reduction and contraceptive counseling will be completed. Adherence of HIV-1 uninfected participants will be measured by self-report and pill counts. In addition, the MEMS cap would be used to complement data generated in the clinic on self-reported pill use. The MEMS cap would generate information on the daily use of pill through electronically capturing data on the frequency of opening the drug bottles. Outcomes of the adherence profile generated from self-reported pill counts and the MEMS cap would be used to counsel patients on how to improve or adhere to drug-use adherence patterns.

Additionally, behavioral and medical history data as well as data on participant preferences regarding antiretroviral-based prevention strategies and fertility intentions will be collected during one-on-one interviews with staff counsellors. Physical examinations for both members of the couple will be conducted. For the woman, physical examination will include pelvic examinations, including naked eye examination of the external genitalia and speculum examination of the vagina and cervix. For males, physical examination will be limited to naked eye examination of the external genitalia.

Syndromic diagnosis and management of STIs will be done. Counseling and clinical care for STIs at the study sites will be in accordance with the Federal Ministry of Health's guidelines. Participants with STIs will be encouraged to refer their partners for treatment.

At enrollment HIV-1 uninfected women will have a pregnancy test to confirm eligibility (must not be pregnant to complete enrollment). Women will be asked about pregnancy at every scheduled follow-up visit and pregnancy testing will be done when clinically indicated (e.g., missed menses, participant request); PrEP will be continued during pregnancy and breastfeeding. In addition, pregnant women will be advised to continue with their follow up visits. When these participants no longer have a positive pregnancy test, the pregnancy outcome will be documented.

Every 6 months, in addition to regular quarterly visit procedures, CD4 counts and plasma viral loads will be done for HIV-1 infected partners.

Clinical safety will be assessed pre-, during- and post-enrollment. Laboratory safety assessments will be done at enrollment, month 12, study exit and additionally if indicated. At these visits, blood samples will be collected for urea, electrolytes, creatinine, liver function tests, full blood count, calcium and phosphate levels.

All HIV-1 infected partners who are interested in starting ART independent of their becoming eligible for ART under the current national guidelines, will be offered ART. Once the HIV-1 infected partner has been using ART for 6 months, PrEP will be discontinued for the HIV-1 uninfected partner, after counseling to the couple.

During follow-up, HIV-1 infected and uninfected participants will complete a quantitative interview to capture evolution in preferences to uptake of antiretroviral-based HIV-1 prevention and fertility intentions and any risk compensation behaviours. Questionnaires will be administered separately to both members of couples.

For participants who are initially uninfected but who seroconvert during the study, PrEP will be discontinued. Their blood specimen will be taken and drug resistance profiling will be conducted. This is to assess if any drug resistance has developed to Truvada and what drug regimen the study participant is sensitive to. Seroconverters will have a visit within 1-month after they seroconvert and then follow-up in the study will be completed for both members of the couple. These visits will include risk reduction and contraceptive counseling, collection of behavioral and medical history data during one-on-one interviews, and collection of blood specimens for assessment of CD4 count, HIV-1 plasma viral load levels from both partners and HIV resistance profiling. Those who seroconvert will be enlisted to have access to ART whenever (s)he is ready to start drug treatment.

Interim visits may occur at any time during the study. All interim contacts and visits will be documented in participants' study records and on applicable CRFs. If a study participant presents to an interim visit with symptoms suggestive of acute HIV-1 infection syndrome, rapid HIV-1 testing will be performed, as at a scheduled visit, and study medication will be withheld if a positive rapid test is documented.

HIV-1 testing for index (HIV-1 infected) participants at screening and for partner (HIV-1 uninfected) participants at screening, enrollment, and follow-up – will be performed in line with national HIV-1 testing algorithms for Nigeria. HIV-1 seroconversions will be

confirmed using HIV-1 EIA. HIV-1 testing will be accompanied by couples and/or individual counseling, depending on attendance of the index (HIV-1 infected) participant at a study visit. All counseling and testing approaches will be in accordance with national HIV-1 counseling and testing guidelines.

Participants infected with hepatitis B virus (HBV) at enrollment will be closely monitored clinically and using laboratory diagnostics especially during episodes of product hold. Any participant needing further treatment for HBV will be referred to a health care provider for further follow-up.

All data collection will be conducted in a private room in the participant's preferred language, according to the participant's fluency and preference.

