programme as this would encourage recruitment of HIV negative females with HIV positive male partners. Recruitment of HIV positive males can also be improved through the use of community-based testing including the use of incentive based testing. Testing should target migrant or mobile work forces like miners and bankers. Care givers who can identify and support couples within the communities for the PrEP program should also be engaged for the programme. It was also important that the programme ensures that drugs and test kits were continuously available at facilities as these are major deterrents to adherence.

In each of the demonstration project States, secondary health facilities should serve as the recruitment and central service delivery point for PrEP clients, while the primary health centers and private hospitals in the state should be engaged to provide drug refills. Recruitment of clients from STI and TB clinics was considered important. Male involvement in the PrEP demonstration project was also viewed as critical. PrEP services should be centralized to the coordinating secondary facility for the first three months which is a critical period in any care program. All data collection process should be centralized. Also, six-monthly laboratory tests to evaluate clients' health profile should be centralized to coordinating secondary health facilities. Drug refills and the 3 monthly HCT should be decentralized to private hospitals and primary care centers. Community engagement programmes activities should also be decentralized. Training on adherence counseling and quality health care service provision needs to be conducted consistently at both centralized and decentralized sites.

Based on the outcome of the deliberations, it was concluded that:

1. In Cross River State, PrEP service should be integrated into the general out-patient health care delivery service structure
2. In Edo State, PrEP service should be centralized to the secondary health care facility
3. In Benue/Plateau State, PrEP service should be decentralized, with central services provided at the secondary health care facility and decentralized services offered at the primary health care facilities.

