## 2.0 Study Method

This is a demonstration project to evaluate the effectiveness of three models for the delivery of PrEP and TasP as part of a combination prevention strategy for serodiscordant couples in three states in Nigeria. The overall goal is to identify the best model to facilitate uptake of PrEP as part of a comprehensive HIV prevention package for the HIV negative partner in serodiscordant relationships whose HIV positive partner has not begun ART or

---

has been on ART for less than six months. PrEP (daily oral FTC / TDF) will be offered to the HIV-1 uninfected partner. Uptake of PrEP and TasP and adherence to PrEP will be measured. Factors (individual, facility and community level) that facilitate PrEP and TasP uptake and adherence to PrEP will also be assessed.

HIV-1 infected participants will be offered the opportunity to use ART support services regardless of their CD4 count. This is in line with the current national guidelines on HIV treatment for adults and adolescents (2010:13). The current guidelines enable HIV positive individuals in discordant relationships to have access to ART irrespective of the CD4 count. This project will therefore serve as a measure of the effectiveness of this program in Nigeria.

For each couple, if the HIV-1 infected partner initiates ART, we will discontinue PrEP for the HIV-1 uninfected partner six months later (once viral suppression is typically achieved). If the HIV-1 infected partner declines to initiate ART, or initiates and discontinues, we will continue PrEP. Mixed-methods work will be conducted to understand user preferences, couples decision-making, and barriers to uptake of and adherence to both PrEP and ART.

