In Cross River State, PrEP will be provided through the outpatients department. The model will evaluate the effectiveness of integration of PrEP service delivery using an integrated approach for access and uptake of both PrEP and TasP services for both HIV negative and the index partners.

In Plateau State, PrEP and TasP will be provided through a decentralized service delivery model. PrEP related service will be obtained from a secondary health facility for the first three months as this is considered a critical period in any care program. Thereafter, services would be decentralized to primary and private project satellite clinics (primary and private centres). The satellite centres will provide the three monthly HCT services and monthly drug refill services. Six monthly laboratory assessment of health profiles would however, be conducted at the central hospital.

In Anambra State however, all PrEP and TasP services will be provided through HIV treatment centres with services remaining centralized.

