### 7.3 For HIV-1 infected members of the couple (index participants)

- Able and willing to provide written informed consent
- HIV-1 infected based on positive rapid HIV-1 tests, according to national algorithm
- No history of WHO stage III or IV conditions
- Not currently using ART
- Currently using ART but viral load still higher than 5000 copies/ml
- Not currently enrolled in an HIV-1 treatment study.
- Current pregnancy or breastfeeding do not disqualify a candidate who is infected.

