## 11.0 Study Procedures

It adopts the Partner's PrEP study approach as discussed at the WHO Demo Meeting in July 2012. The anticipated total study duration is approximately 24 months, with accrual requiring approximately 6 months and follow-up continuing for approximately 18 months after the end of the accrual period. Potential study participants will be screened for eligibility and eligible participants will be enrolled in the study within 30 days of screening. Visits will take place at screening and enrollment, a visit 1 month after enrollment, and then quarterly thereafter, for up to 18 months.

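### Under Section 11.5 as written, PrEP users whose partner starts ART early and stays on it have no scheduled on-drug safety panel after baseline, and the six-monthly tests in Section 2.0 are not reconciled with that schedule

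*Protocol*

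**What the plan says.** Section 11.5 schedules the safety panel, which covers renal and liver chemistry, electrolytes, blood count, calcium and phosphate: "Laboratory safety assessments will be done at enrollment, month 12, study exit and additionally if indicated". The only six-monthly tests in that section are CD4 count and viral load, for the infected partner.

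The same section sets the stopping rule: "Once the HIV-1 infected partner has been using ART for 6 months, PrEP will be discontinued for the HIV-1 uninfected partner". Section 2.0 has the same rule and adds the exception: "If the HIV-1 infected partner declines to initiate ART, or initiates and discontinues, we will continue PrEP".

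Early ART is a planned route. Section 11.5 says that at enrollment infected partners "will be offered TasP, or referred/initiated on ART if they are eligible at the time of enrollment", and later offers ART to every infected partner who wants it. Section 11.0 sets the visits as "a visit 1 month after enrollment, and then quarterly thereafter, for up to 18 months".

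Two other places mention six-monthly laboratory work. In Section 2.0, within the description of the decentralized Plateau model: "Six monthly laboratory assessment of health profiles would however, be conducted at the central hospital". In Section 1.8, which reports planning consultations: "Also, six-monthly laboratory tests to evaluate clients' health profile should be centralized to coordinating secondary health facilities". Neither says which tests are meant, and Section 11.5 refers to neither.

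**The concern.** The panel calendar runs from enrollment, while the length of PrEP exposure is set by the partner's ART start. Nothing ties the two together. Couples who take up ART promptly, as the staged strategy intends, can finish PrEP before the first post-baseline panel falls due. Their month-12 value then describes someone already off the drug, and could be read as an on-drug value if the analysis does not separate the two.

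Section 1.5 names safety monitoring in users as something the project should inform before roll-out, and Section 5.0 asks whether integrated delivery reaches levels of safety similar to those in the trials. The couples who follow the PrEP-then-ART sequence fastest would contribute no scheduled laboratory value to either question. A statistical analysis plan cannot recover a sample that was not drawn.

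**Working it through.** There is no sample size or power figure to reproduce here; the check is of timing.

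**Inputs.** Panels at months 0, 12 and exit (Section 11.5). PrEP stops 6 months after ART start if ART continues (Sections 2.0 and 11.5). Exit is taken as month 18, the maximum follow-up in Section 11.0. A panel drawn on the day PrEP stops counts as on-drug.

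**Prompt stop.** With ART started at month t and continued:

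- PrEP stop = t + 6
- month-12 panel on drug if 12 ≤ t + 6, that is t ≥ 6
- time from stop to the month-12 panel = 12 − (t + 6) = 6 − t
- time from stop to a month-18 exit panel = 18 − (t + 6) = 12 − t

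| ART start t | PrEP stop | Scheduled on-drug panels after baseline | Stop to month 12 | Stop to month 18 |
|---|---|---|---|---|
| 0 | 6 | 0 | 6 | 12 |
| 3 | 9 | 0 | 3 | 9 |
| 5 | 11 | 0 | 1 | 7 |
| 6 | 12 | 1 (month 12) | 0 | 6 |
| 9 | 15 | 1 (month 12) | – | 3 |
| none | 18 | 2 (months 12, 18) | – | – |

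If follow-up is only 12 months, exit coincides with month 12 and the cut-off at t = 6 does not move.

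**Stop delayed to the next quarterly visit.** Take visits at months 3, 6, 9 and 12 (an assumption; see below). The stop becomes t + 6 rounded up to the next multiple of 3:

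- t = 0: stop at 6
- t = 1 or 3: stop at 9
- t = 3.1, 4, 5 or 5.9: stop at 12, so the month-12 panel is on drug

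Starts up to month 3 therefore still have no scheduled on-drug panel; later starts do.

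**Visit grid.** Section 11.0 can also be read as months 1, 4, 7, 10 and 13. A delayed stop then falls at month 10 or earlier when t + 6 ≤ 10, that is t ≤ 4, so the group that misses the panel is no smaller. On either grid visits are 3 months apart, so a scheduled visit always falls less than 3 months before a prompt stop.

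**If the six-monthly tests are this panel.** A month-6 draw is on drug when 6 ≤ t + 6, which holds for every t ≥ 0. Each user with 0 ≤ t < 6 then has one on-drug panel and the gap closes.

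**The case against.** The strongest reply is that the protocol may already provide the missing draw. In Section 2.0 the Plateau sentence contrasts place, not frequency: refills and HIV testing move to satellites while laboratory work stays central. Read that way, it presupposes a six-monthly schedule. If that schedule is the Section 11.5 panel and applies at every site, nothing is missing. The content may also sit in the laboratory plan or procedures manual, which are not at hand. This stands as a reason for caution. It does not settle the matter, because the sentence is firm only for Plateau, names no tests, and is absent from the section that governs monitoring.

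Second, PrEP may not stop on the exact day. Section 11.5 puts counseling of the couple before stopping, and Section 11.3 dispenses enough drug to last until the next visit. This also stands, and it is why starts between months 3 and 6 are only conditionally affected.

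Third, no measure listed in Section 3 is a laboratory safety measure, and users whose partner starts ART later or never still supply on-drug panels. That is true and limits the importance of the point.

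Three stronger readings are tempting, and the protocol does not support them.

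- A reader might infer that early-ART couples are exposed to extra risk. Under Section 11.5 nobody has a scheduled panel between enrollment and month 12, so while on drug these users are monitored like everyone else, and for a shorter time. Entry requires adequate renal function (Section 7.2), extra tests are allowed when indicated, and participants with hepatitis B have closer laboratory follow-up (Section 11.5).
- A reader might treat Section 1.8 as a contradiction across all sites. It is a background recommendation from planning meetings and names a state, Edo, that is no longer a site. That sites will in fact follow different schedules is not shown.
- A reader might extend the gap to index partners already on ART at entry, since Section 7.3 admits someone "Currently using ART but viral load still higher than 5000 copies/ml". Section 2.0 describes the target group as having had under six months of ART, and the protocol does not say how earlier ART counts toward the rule. Any figure for this group would rest on stacked assumptions, so it is left out.

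**Conclusion.** The point holds with limits. If Section 11.5 governs, a user whose partner starts ART before month 6 and continues it has 6 to just under 12 months of PrEP under a prompt stop, and no scheduled on-drug safety panel after baseline. For starts before about month 3 this follows whether PrEP stops promptly or at the next quarterly visit. For starts between months 3 and 6 it requires a prompt stop.

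The conclusion assumes that the user remains in the study on the planned course (leaving early while on PrEP could bring an on-drug exit panel) and that no unscheduled test is done. It would fall away if the six-monthly assessments were declared to be this panel at every site. The number of users affected cannot be given, because the protocol states no expected ART uptake.

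What is lost is on-drug laboratory data from couples who follow the intended sequence quickly, together with clarity about which laboratory schedule applies. It is worth correcting because the correction is cheap, not because a hazard has been shown.

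**What to change.** Amend Section 11.5 so that, at all three sites, a user whose PrEP is stopped before month 12 under the 6-month ART rule has the safety panel drawn at the PrEP-stop visit or at the last scheduled visit while still on PrEP. Tying the draw to the stop avoids relying on a particular visit grid.

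State in Section 2.0 whether the six-monthly assessments are this panel and whether they apply at every site. If they are and do, correct the Section 11.5 schedule to match.

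The cost is a wording amendment to Section 11.5 and one clarifying sentence in Section 2.0. No new visit is needed, because scheduled quarterly visits can carry the draw. The downside is that one routine panel is moved, so the later off-drug month-12 value is lost for these users, or one panel is added if that value is kept.

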#### 11.6 Co-enrollment guidelines

Participants in this study may not take part in any other concurrent research studies that would interfere with the objectives of this study. The determination of whether participation in another study would be exclusionary for a given participant will be made by the Principal Investigators. Approved co-enrollment in other concurrent protocols will be documented.

#### 11.7 Participant retention

The Protocol Team will track retention rates. Once a participant is enrolled in the study, study staff will make every reasonable effort to ensure adequate locator information is available for follow-up tracking. Participants will be reminded of their clinic visits using sms messages sent on their telephones. A missed visit will prompt a single telephonic reminder, where the participant is spoken to directly and reminded of the clinic visit. A maximum of 3 reminders will be made. Retention efforts will be standardized across study sites.

#### 11.8 Participant withdrawal

Participants may voluntarily withdraw from the study for any reason at any time. Designated study staff may also withdraw participants from the study in order to protect their safety. Participants may also be withdrawn if the National Ethics Committee terminates the study prior to its planned end date. Every reasonable effort will be made to complete a final evaluation of participants who withdraw or are withdrawn from the study. Study staff will record the reason(s) for all withdrawals in participants' study records.

#### 11.9 Adherence counseling and case management

Adherence counseling will be provided to study participants upon enrollment and additionally at each study visit. Adherence counselors / nurses will be provided with a set of job aids, including a reference guide to assist with and standardize adherence support counseling. Techniques based on motivational interviewing will be used to address such topics as participant-centered strategies to remember to use the products daily, to ensure the availability of the products both in the home and away from home, and to identify and discuss various challenges and situations that may impede product use. Counseling will include reminders to contact study staff with questions about PrEP use and requests for

additional supplies. For participants experiencing adherence challenges, every effort will be made to identify customized strategies to increase their rates of product use throughout the course of the study. Data on adherence will be collected at each study visit via brief interviewer administered instruments.

